#### Exclusion criteria

Participants who experience cybersickness during the familiarization session and those who miss the first two consecutive sessions will be excluded. Additionally, participants must complete 100 % of the training sessions to remain in the study. They may miss up to 20 % of the sessions, provided that all missed sessions are made up through compensatory sessions, to be scheduled in agreement with the research team.

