### Assessments

A trained researcher will provide the participant with an informed consent form. The same researcher, blind to the treatment allocation, will assess all participants at two-time points: before and after the interventions. Participants will be asked not to inform the evaluators about the type of intervention they received.

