### Sample size

The sample size calculation was based on a review with meta-analysis regarding the effectiveness of VR for individuals with mild cognitive impairment or dementia, which produced small to medium effect sizes using a random effects model (effect size = 0.29) from a total of 11 studies.^36^ Assuming a dropout rate of 20 %, a total sample size of 32 participants (16 per treatment group) would provide a power of 0.8 with a two-tailed α error of 0.05.

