### Data analysis

Continuous variables will be presented as mean and standard deviation, while categorical variables will be expressed as absolute frequencies (n) and percentages ( %). The distribution of the data will be assessed using the Shapiro-Wilk test. The Z-score will be used to normalize non-parametric data. Continuous data will be analyzed using the General Linear Model (GLM) for repeated measures and univariate GLM for group comparisons. The effect size and 95 % Confidence Interval will be reported along with their interpretations. The significance level will be set at α ≤ 0.05, and when applicable, clinical details related to the instruments, such as the minimum detectable change and measurement error, will also be included. Data analyses will be conducted using SPSS version 24.0.

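### The repeated-measures GLM compares unadjusted change scores in participants with both scores; a baseline-adjusted final score is more precise and less exposed to baseline-related dropout

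*Protocol article*

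**What the plan says.** - **Model.** Under Data analysis: "Continuous data will be analyzed using the General Linear Model (GLM) for repeated measures". The same sentence also names a univariate GLM for comparing the groups. The section does not say which of the two models carries the comparison between arms, and it names no baseline covariate for either. It adds: "Data analyses will be conducted using SPSS version 24.0".
- **Assessments.** Under Assessments, one blinded researcher "will assess all participants at two-time points: before and after the interventions". There is no intermediate score.
- **Expected loss.** Under Sample size: "Assuming a dropout rate of 20" per cent, with "a total sample size of 32 participants (16 per treatment group").
- **Retention.** Under Exclusion criteria, participants must complete all "of the training sessions to remain in the study", with missed sessions made up. The article does not say that a participant who stops training is still assessed at the end.

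**The concern.** With two assessments, a repeated-measures GLM needs both scores from each participant. Its group-by-time F test is the square of a two-sample t test on final minus baseline. Two things follow.

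First, subtracting the whole baseline score is inefficient unless the pre-post correlation is close to 1. Adjusting for baseline by regression uses the same data and gives a smaller standard error.

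Second, a change score carries regression to the mean. If low scorers leave one arm more than the other, the remaining participants start from different average baselines and regress by different amounts, which appears as a group-by-time effect when there is none.

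At stake is the hypothesis that virtual reality improves motor, cognitive and mood outcomes more than the exercise comparator, in a trial where about 6 of 32 participants are expected to be lost.

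**Working it through.** **1. The plan's own figure.** N = 32 can be reproduced if 0.29 is read as Cohen's f for a group-by-time interaction with 2 groups, 2 times and an assumed correlation of 0.5. The noncentrality is f² × N × 2/(1 - 0.5) = 0.0841 × 26 × 4 = 8.75, which gives power 0.81 at N = 26. Inflating for dropout gives 26 × 1.2 = 31.2, so 32, or 26/0.8 = 32.5, so 33. In the other direction, 32 × 0.8 = 25.6. The sample size is therefore consistent with about 26 analysed participants, 13 per arm. The article states neither the metric of 0.29 nor the correlation.

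**2. Illustrative scenario (assumptions, not from the article).** There is no true effect, and scores have SD 1 at both times with correlation ρ. Each arm has 16 participants and loses 3. In one arm the 3 lost are the lowest on baseline plus noise of SD 0.7; in the other they are lost at random.

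**3. Shift in baseline among those who remain.** The three lowest of 16 standard normal values have expected values -1.766, -1.285 and -0.990, which sum to -4.041. The other 13 therefore average 4.041/13 = 0.311. The correlation of baseline with the noisy selection variable is 1/√(1 + 0.49) = 0.819. The baseline shift is δ = 0.311 × 0.819 = 0.255 SD.

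**4. Bias when dropout depends on baseline.** The expected final score given baseline b is ρb, so the expected change is -(1 - ρ)b.
- Change score: -(1 - ρ)δ = -0.127, -0.076 and -0.051 at ρ = 0.5, 0.7 and 0.8.
- Baseline-adjusted: 0, because the regression on baseline is the same in both arms.

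**5. Simulation check (40,000 trials per correlation).** Both analyses use exactly the same 26 participants.

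| ρ | Bias, change | Bias, adjusted | SE, change | SE, adjusted | SE reduction |
|---|---|---|---|---|---|
| 0.5 | -0.128 | 0.001 | 0.391 | 0.352 | 10% |
| 0.7 | -0.074 | 0.001 | 0.303 | 0.291 | 4% |
| 0.8 | -0.050 | 0.001 | 0.248 | 0.243 | 2% |

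The false-positive rate at nominal 5% is 6.5%, 5.9% and 5.6% for the change score, and 5.1% to 5.2% for the adjusted contrast.

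**6. The unfavourable case: dropout depends on the final score.** The setting is otherwise the same. The change-score bias is +(1 - ρ)δ. The adjusted bias is about δ - ρ(ρδ) = (1 - ρ²)δ, larger by a factor of about 1 + ρ. The false-positive rate is in brackets.

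| ρ | Change, formula | Change, simulated | Adjusted, formula | Adjusted, simulated |
|---|---|---|---|---|
| 0.5 | +0.127 | +0.124 (6.3%) | +0.191 | +0.194 (9.4%) |
| 0.7 | +0.076 | +0.076 (5.7%) | +0.130 | +0.137 (8.2%) |
| 0.8 | +0.051 | +0.052 (5.7%) | +0.092 | +0.101 (7.3%) |

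Adjustment removes the first kind of bias and makes the second kind worse.

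**The case against.** **Deleting incomplete participants is not the cause.** A reader might infer that the fault is the removal of everyone without a final score, and that a mixed model is needed to keep them. Step 5 shows otherwise: the adjusted analysis omits the same six people and has almost no bias. With two assessments, a participant with a baseline score alone adds essentially nothing to the final-score contrast. The gain comes from baseline adjustment, and the univariate GLM already named can supply it. This objection stands in full.

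**The alternative can do worse.** Step 6 bears this out. It does not favour change scores, which are also biased there, but it rules out presenting adjustment as a complete remedy.

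**The mechanism is assumed.** A reader might infer that cybersickness gives the virtual reality arm its own route to loss. The article ties that exclusion to a familiarization session without limiting it to one arm or placing it before or after allocation. It also excludes people with motion sickness at entry. Nothing in it links cybersickness to low baseline scores.

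**The size is easily overstated.** Expressing the bias as a share of 0.29 would treat 0.29 as an SD difference. The article does not say so, and N = 32 was reproduced only with 0.29 as Cohen's f. In the illustration the bias is 0.2 to 0.3 of one standard error, and the article calls the study preliminary.

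**Missing-data handling may sit in a fuller plan.** That is so, and its absence here is not the point. The point concerns the named model and the stated retention rule.

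**Conclusion.** The point holds in a limited form. With two assessments, the named repeated-measures GLM is an unadjusted change-score comparison in participants with both scores. Adjusting for the baseline already collected improves precision by about 2% to 10% in standard error over correlations of 0.8 down to 0.5. It also removes a bias of about 0.05 to 0.13 SD in the scenario where low scorers leave one arm. These figures rest on an assumed dropout pattern, equal variances and assumed correlations, so they show what can happen and do not predict this trial. That the change-score test omits participants without a final score is a property of the procedure and is not written in the article.

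The retention rule adds to the problem. It takes participants who stop training out of the study, although a final assessment is already scheduled. Collecting their final scores is the only step discussed here that lowers the risk under both dropout mechanisms.

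**What to change.** 1. Under Data analysis, define the between-group contrast as the final score adjusted for baseline. Fit it either as the univariate GLM already named, with baseline as covariate, or as an equivalent mixed model with a common baseline mean. Include all randomised participants with a final score, in the arm to which they were allocated.
2. Under Exclusion criteria, reword the rule so that participants who stop training are still invited to the scheduled final assessment and are analysed as randomised.
3. Add one sensitivity analysis that applies arm-specific shifts to missing final scores over a stated range, because the main analysis does not protect against dropout that depends on the unseen score.

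**Cost.** The analysis change is wording and one extra table in the same software. The retention change needs the formal amendment described under Protocol amendments and some effort to bring people back. With about half of participants already recruited, it may come too late for some who have left. The remaining downside is that the main analysis relies on final scores being missing at random given baseline and arm.

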### Hypotheses

1.VR interventions will significantly improve postural control, gait, functionality, cognition, and mood more than the motor-cognitive integrated intervention.2.The authors hypothesize that participants undergoing VR interventions will improve their performance in the games.3.The authors expect that commercial VR games will be acceptable to older adults with mild NCD or mild major NCD. Although this population may not be familiar with this technology, commercial games were developed for entertainment in an attractive and motivating virtual environment and were easy to use.

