### Outcome measures of acceptability

Feasibility will be assessed by the participant's game performance, measured by the scores achieved. Increasing scores indicate that the participant can play and improve their performance in the games. It is the primary measure of the game that promotes motivation.^26^ Acceptability will be evaluated through a game satisfaction questionnaire. The questionnaire consists of nine questions, including participants' perceptions of the games (“What did you think of the game?”; “Would you recommend this game?”; “Would you play this game at home?").

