### Clinical outcome measures

Table 3 shows the assessments used as Clinical Outcome Measures.

**Table 3 tbl0003:** Clinical outcome measures and assessments.

Clinical outcome	Assessment
Postural control	Mini-BESTest^27^
Gait	Dynamic Gait Index^28^
Cognitive functions	Neurocognitive Battery of SGHC-FMUSP; Word Accentuation Test^29^; MoCA (Montreal Cognitive Assessment)^30^
Functionality	Functional Activities Questionnaire^31^
Mood	Generalized Anxiety Disorder 7-item^32^; Patient Health Questionnaire-9^33^
Manual dexterity	Box and Blocks^34^
Strength	Hand Grip Test^35^

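### A superiority hypothesis over five domains, a power claim and one 0.05 level are fixed with no primary outcome among ten instruments: about 29–40% risk of a false difference either way, 15–22% favouring VR

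*Protocol article*

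**What the plan says.** - **Hypotheses.** The first hypothesis is that "VR interventions will significantly improve postural control, gait, functionality, cognition, and mood more than the motor-cognitive integrated intervention". It names five domains and gives no rule for what counts as confirmation.
- **Clinical outcome measures.** "Table 3 shows the assessments used as Clinical Outcome Measures". Table 3 has seven outcomes and ten named instruments: Mini-BESTest, Dynamic Gait Index, a neurocognitive battery, Word Accentuation Test, MoCA, Functional Activities Questionnaire, GAD-7, PHQ-9, Box and Blocks, and Hand Grip. None is marked primary. The cognitive row includes "Neurocognitive Battery of SGHC-FMUSP; Word Accentuation Test", and the number of scores in the battery is not given. Manual dexterity and strength are outcomes but appear in no hypothesis.
- **Sample size.** The basis is a meta-analysis "which produced small to medium effect sizes using a random effects model (effect size = 0.29"). Power of 0.8 is claimed "with a two-tailed α error of 0.05" for 32 participants. No outcome is named.
- **Data analysis.** "Continuous data will be analyzed using the General Linear Model (GLM) for repeated measures and univariate GLM for group comparisons", followed by "The significance level will be set at α ≤ 0.05". There is no ordering of outcomes.
- **Outcome measures of acceptability.** The word primary appears only here, about game scores: "It is the primary measure of the game that promotes motivation". That does not designate a trial endpoint.

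**The concern.** A superiority hypothesis, a power statement and a significance level all need an outcome to refer to, and here none has one. Even within a domain the deciding measure is open: cognition has three entries and mood has two.

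Two things follow. First, if Table 3 is worked through at 0.05 per instrument, the chance of some false significant difference is well above 5%. Second, once results are known, the article gives no basis for saying which of them settles Hypothesis 1. A mixed set of results could be read as support or as failure. The Discussion expects the comparison to show which approach may be more effective and to inform clinical practice and health policy, so the deciding outcome matters even in a small trial.

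**Working it through.** **Inputs from the article**
- Ten named instruments, eight of them in the five domains of Hypothesis 1 (Table 3, Hypotheses).
- Two-tailed 0.05 (Sample size), so 0.025 per test in the direction favouring VR.
- 16 per arm and 20% dropout (Sample size): 16 × 0.8 = 12.8, about 13 per arm analysed.

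**Assumptions**
- Each instrument gets one group comparison at two-sided 0.05.
- There is no true effect on any instrument.
- The correlation between outcomes is the same for all pairs. The article gives no value, so 0 to 0.5 is shown.

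**The plan's own figure.** The article states no familywise error rate. Its only computed figure is N = 32. That is reproduced under one set of unstated choices: 0.29 read as Cohen's f, a group-by-time interaction with two groups and two time points, and a pre–post correlation of 0.5. This gives N = 26 (power 0.81), then 26 × 1.2 = 31.2, rounded up to 32, or 26/0.8 = 32.5, rounded up to 33. Read as a standardised mean difference, 0.29 needs 187 per arm before dropout. Neither reading identifies an outcome, and the error rates below do not depend on which one is right.

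**Independent tests**
- Either direction, 10 instruments: 1 − 0.95^10 = 0.401
- Favouring VR, 10 instruments: 1 − 0.975^10 = 0.224
- Either direction, 5 domains with one test each: 1 − 0.95^5 = 0.226
- Favouring VR, 5 domains: 1 − 0.975^5 = 0.119

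**Correlated tests** (simulated two-sample t-tests, 13 per arm)

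| Tests | Direction | r = 0 | r = 0.3 | r = 0.5 |
|---|---|---|---|---|
| 10 | either | 40% | 35–36% | 29% |
| 10 | favouring VR | 22% | 18% | 15% |
| 8 (instruments under Hypothesis 1) | either | 34% | 30% | 25% |
| 8 | favouring VR | 18% | 15% | 13% |
| 5 (one per domain) | either | 23% | 21% | 18–19% |
| 5 | favouring VR | 12% | 11% | 9% |

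With two time points, the group-by-time test in a repeated-measures model is a t-test on change scores, so this simulation fits the planned analysis.

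**Comparison.** One primary outcome at two-sided 0.05 gives 5% in either direction and 2.5% favouring VR. Ten instruments therefore carry about 29/5 = 6 to 40/5 = 8 times the either-direction risk. For a false VR advantage the ratio is about 15/2.5 = 6 to 22/2.5 = 9.

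Counting the battery's scores separately would raise the figures, but the article does not say how many there are.

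**The case against.** Several points on the other side have weight.

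- **A multiplicity method may be in an analysis plan that is not shown.** This stands, and the absence of an adjustment is not the point made here. The outcome to which a superiority hypothesis and a power claim refer is a different matter. The article has sections on hypotheses, outcomes, sample size and analysis, and none of them names it.
- **The work is preliminary.** The Dissemination policies section says it is meant to inform a later definitive trial, and the Data analysis section already commits to effect sizes and 95% confidence intervals. Both reduce the consequence. Neither removes a hypothesis worded as significant superiority.
- **No rule says that one significant instrument is enough.** A reader might infer such a rule, but Hypothesis 1 joins its five domains with *and*. If all five had to succeed, the error would not inflate. The article states neither rule. Testing each instrument separately at 0.05 is likewise an inference from the Data analysis section, though the natural one.

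Two stronger readings are tempting and are not supported.

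- **A 30–40% chance of a false VR advantage.** With a two-tailed level, that range covers false differences in either direction, including those favouring exercise. For ten tests the chance of one favouring VR is at most about 22%.
- **Power of only about 11% per outcome, so that an isolated significant result is probably spurious.** The 11% holds only if 0.29 is a standardised mean difference compared post-intervention with 13 per arm. The article does not give the scale and plans a repeated-measures model.

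**Conclusion.** The point holds as a defect in what the article fixes: superiority in five domains, power of 0.8 and a single 0.05 level, with no primary outcome among ten instruments and no rule for deciding Hypothesis 1.

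Under one two-sided 0.05 test per instrument and no true effect, the chance of at least one false significant difference is about 29–40% in either direction and about 15–22% in favour of VR. For one test per hypothesised domain it is about 18–23% and 9–12%. The ranges rest on assumed correlations of 0 to 0.5, and higher correlations would give lower figures. Given the trial's stated preliminary purpose, this should be fixed but is not disqualifying.

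**What to change.** Before any unblinded comparison, amend the protocol as follows:

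1. The investigators name one clinical outcome that is already collected as primary. A global cognitive score is one candidate, since the sample-size source is a meta-analysis in people with cognitive impairment or dementia. Nothing in the article singles out a particular instrument, so the choice is theirs. If the registry record, which was not available for this review, already names a primary outcome, the protocol should be reconciled with it.
2. Tie Hypothesis 1 and the sample-size statement to that outcome, and claim superiority only on it, at two-sided 0.05.
3. Report the other Table 3 outcomes as secondary, with the effect sizes and 95% confidence intervals already planned. Use Holm-adjusted p-values if significance is claimed for any of them.

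The cost is a short amendment through the route the article already describes, with the registry updated where needed. No participant procedure changes. About half the participants had been recruited when the article was written, so the choice can still be made without knowledge of group results if no unblinded comparison has taken place. The downside is that fewer outcomes can be called significant.

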### Adverse events

An adverse event is defined as any undesirable medical occurrence in a participant that does not necessarily have a causal relationship with this intervention. The study team will review any adverse events, assess probable causality, and report on a form.

### Audit

The authors will establish a rigorous quality control program. A trained team and the trial coordinator will ensure adherence to the trial protocols. The University of São Paulo will conduct quality assurance checks to ensure the integrity of randomization, study entry procedures, and data collection.

### Protocol amendments

Any modifications to the protocol that may impact the conduct of the study, potential benefits to the participant, or that may affect participant safety ‒ including changes to study objectives, study design, participant population, sample sizes, study procedures, or significant administrative aspects ‒ will require a formal amendment to the protocol. Such amendments will be agreed upon by the Ethics Committee of the Faculty of Medicine, University of São Paulo, Brazil, and the Brazilian Clinical Trials Registry before implementation and reported to health authorities in accordance with local regulations.

### Dissemination policies

The dissemination will aim to inform a wide range of local, national, and international audiences about the results and conclusions. However, it should be remembered as part of this strategy that the current project is a preliminary work intended to inform a subsequent definitive clinical trial. The goal is to publish the present research in journals that cover relevant medical specialties, preferably those that deposit publications in open-access databases to enhance free dissemination. Additionally, the authors aim to present this research at appropriate national and international conferences.

## Discussion

The current study will compare the effects of VR games with a motor-cognitive integrated intervention on cognitive and motor outcomes in NCD participants. The choice of commercial games as an intervention is justified by their accessibility and potential to engage older adults in a playful manner, promoting social interaction and enjoyment. The literature already suggests that games can improve cognitive functions, not only overall cognitive scores but also memory, attention, and processing speed, along with offering motor benefits.^37^ Several studies consider cognitive-motor training to be a beneficial training method leading to greater cognitive and motor improvements and is essential for better understanding which intervention may be more effective and well-accepted.^38^

Acceptability is a crucial factor for the sustainability of any intervention program. Older adults are expected to feel more motivated to participate in activities that are perceived as enjoyable and stimulating. However, it is also essential to consider the barriers that may arise; all health disciplines should challenge age bias and embrace and support the use of technology by older adults, promoting digital inclusion for these individuals.^39^

The expected results of this study may significantly contribute to the formulation of intervention strategies more suited to the needs of older adults, promoting healthy and active aging. Furthermore, comparing interventions will allow for identifying approaches that may be more effective in managing NCD and mild major NCD, providing directions for future clinical practices and public health policies.

